**Project Summary:**

Recently, it was demonstrated at UCLA that trigeminal nerve stimulation (TNS) is safe and effective in treating pediatric ADHD. TNS is a noninvasive, non-pharmaceutical, minimal-risk, low-current neurostimulatory therapy for ADHD. TNS is now FDA-cleared for children with ADHD not currently taking ADHD medication. The FDA-clearance makes no distinction with respect to the etiology of the ADHD, but the possible influence of etiology on TNS response has not yet been systematically investigated. One of the major etiologies of ADHD is prenatal alcohol exposure (PAE). To our knowledge, TNS has never been systematically tested in children whose ADHD is likely due to PAE. Here we propose the first clinical trial of TNS for children with ADHD associated with PAE. There is a pressing need for such a study as ADHD is very common in PAE, ADHD symptoms are among the most disabling in PAE, and children with PAE frequently respond poorly to conventional pharmaceutical treatments (i.e, psychostimulants) for ADHD. PAE, moreover, is a severe, life-long neurodevelopmental disorder. It afflicts hundreds of thousands of children in the US and worldwide and treatment options are few. Therefore, it is incumbent to explore every reasonable prospective treatment in children with PAE, particularly TNS. Based on our prior neuroimaging studies of ADHD in PAE, we are optimistic that TNS will be efficacious in relieving ADHD symptoms, as we have seen abnormalities in the brains of children with ADHD due to PAE in the same brain regions that TNS is thought to act upon in EEG studies. But there is a chance TNS might not be effective, therefore it must be tested explicitly. Children with PAE are very frequently prescribed psychotropic medication, to the point where it would not be feasible to recruit a sufficiently large sample size within the study term if medicated children were excluded. Therefore, this study will include children who are on ADHD medication. Since some subjects will be medicated, the study overall will **not** be within current labelling of the TNS device. Therefore, as per standard UCLA IRB policy, based on his Initial Assessment, the PI made a determination that the study TNS device is a non-significant risk (NSR) device. The IRB has agreed with this determination. Rather than "use of an FDA-cleared device for an approved indication" it has classified the research as "investigational use of an NSR device". This classification was granted for the Generation 1.0 TNS device which we plan to use in this study. The manufacturer, however, will phase-out the Gen 1 device and replace it with a Generation 2.0 TNS device as of January 2025. The Gen 2 device is highly similar to Gen 1; in particular, it delivers the same electrical stimulation waveform to the patient. The PI has also requested an NSR classification for the Generation 2.0 TNS device to use in this trial, in case it is needed to replace damaged or lost Gen 1 devices.

This IRB proposal is associated with our R61/R33 grant proposal (currently pending funding approval at NIAAA). The R61 (pilot) phase will determine whether TNS is feasible for PAE: Do children with PAE comply with TNS procedures? Does TNS have any serious side effects in these children? Is there an indication that TNS relieves symptoms of PAE? Is such relief retained in follow-up? If the pilot shows feasibility, as we expect it will, we will be in a position to apply for continued funding of an R33 phase. In that R33, we would conduct a formal double-blind sham-controlled randomized clinical trial to determine rigorously whether TNS is truly efficacious for PAE. The present IRB proposal concerns only the R61 phase. If the R33 is later funded, we will submit an amended proposal to the IRB at that time. If TNS is efficacious for PAE, the impact could be enormous. TNS could bring much needed relief to children with PAE and their families everywhere. Our proposal, furthermore, will address the need to understand the brain mechanisms by which TNS works. These are underexplored and largely unknown for ADHD or any condition treated by TNS. The few studies done to date point to three major candidate brain regions where TNS may exercise its therapeutic effects. All three are regions where

we, in prior work, detected differences between children with PAE and typically developing children in tissue properties (“endpoints”) measured using multiple different varieties (“modalities”) of brain MRI. These imaging findings raise our confidence that TNS will be effective for PAE. I.e., if the brain regions that produce PAE symptoms are the same as those acted upon by TNS, maybe TNS will quell those symptoms. In both phases of this clinical trial we will measure the same endpoints with the same modalities of brain MRI in children with PAE before and after TNS treatment. We will determine whether these endpoints are changed by TNS (target engagement) and/or predict TNS clinical response (prognostic marker) in individual patients in the three candidate regions or elsewhere in the brain. If successful, this proposal will help meet a long-standing urgent need for novel treatments for PAE and will help clarify the currently mysterious brain mechanisms of an emerging pediatric neurostimulatory therapy.

## Background

Prenatal Alcohol Exposure (PAE) still affects more than 5% of US children despite decades of public efforts to curb ethanol consumption during pregnancy. High disability arises from the ADHD-like behavioral symptoms (hyperactivity, impulsivity, executive function deficits) that occur in 50-95% of children with PAE. In ADHD, these symptoms often improve spontaneously by adulthood. But in PAE they typically evolve into lifelong problems in attention and executive function, behavioral and emotional regulation, and adaptive function. These problems contribute to “secondary disabilities”, i.e., adverse outcomes including school failure, legal trouble, substance abuse, mental illness, and suicide frequently encountered by people with PAE in adolescence and adulthood. Secondary disabilities add to the >\$4 billion/year public health cost of PAE. Formal treatment studies for PAE are lacking. Psychostimulants are commonly prescribed for behavioral symptoms in both ADHD and PAE. While these drugs, however, lead to routine improvement in ADHD, their efficacy in PAE is not well established. Rather, there is much evidence that stimulants are less effective for PAE. Side effects to stimulants, moreover, may occur at higher rates in PAE. While promising evidence-based behavioral interventions for PAE have emerged at UCLA and elsewhere, children with PAE often fail to retain gains achieved with behavioral therapies. Thus, there are currently no truly effective treatment options for PAE. This proposal aims to address this urgent unmet need by conducting a pilot (R61) clinical trial of a novel treatment for behavioral symptoms of PAE.

Trigeminal nerve stimulation (TNS) was recently found safe and efficacious for core (inattention, hyperactivity) and executive-function symptoms of ADHD in unmedicated children in an open pilot and a sham-controlled double-blind randomized controlled trial (RCT) at UCLA (McGough et al. 2015,2019). The response rate (50%) was appreciable for psychiatry, comparable to the 40-60% efficacy of SRIs for major depressive disorder. While these trials led to FDA-clearance of TNS for unmedicated pediatric ADHD, patients in those trials were not screened for PAE. Given the symptom overlap of PAE and ADHD and the fact that certain putative sites of action of TNS in the brain match sites where we found imaging abnormalities in PAE, we are optimistic that TNS will also be safe and effective in alleviating the behavioral symptoms of PAE. But formal testing of this expectation is required if we are to have a firm basis for recommending TNS as a therapy for PAE. There is a chance that TNS might not be safe or effective for PAE. Stimulant drugs, as mentioned, usually work for ADHD but often not for PAE. Also, our preliminary data acquired with magnetic resonance (MR) neuroimaging has documented differences between children with ADHD-like symptoms with and without PAE in many brain regions. Such differences may influence clinical response to TNS, in positive or negative ways. A clinical trial with imaging may answer this question and help elucidate the therapeutic mechanism of TNS which (although we have some clues) is unknown for any of the conditions that it treats. Our clinical trial will test TNS for the first time in children with known PAE and will include imaging to identify brain regions that are changed by TNS and/or that predict TNS response. This trial of TNS for PAE was thus submitted under the NIAAA R61/R33 mechanism, which is designed for novel therapies, with perhaps partly understood mechanisms, holding promise for success, but with a need for rigorous testing.

The FDA-clearance for the TNS device covers only children with ADHD who are not currently taking ADHD medication. Children with ADHD associated with PAE are not specifically excluded by the labelling, nor are they specifically included. This proposal will test the TNS device in children with ADHD associated with PAE, some of whom will be taking concurrent

ADHD medication. Based on our Initial Assessment, we do anticipate additional risks due to medication and we will not ask parents to take their children off medication. Thus, TNS treatment, at least for children on medication, will be off-label. Therefore, rather than as “treatment with an FDA-cleared device within an approved indication”, present research is classified as “investigational use of an NSR device”.

Potential impact is very high. If TNS is safe and efficacious for PAE, this proposal will yield a much needed new therapy for managing PAE. Study data could possibly be used to apply for an expanded FDA-clearance that specifically lists PAE as an indication and that allows treatment of medicated children. Of the 49.5 million school-age children in the US, if one takes the low estimates that 1.8% have PAE, 50% of these have ADHD-like symptoms, and 50% of these respond to TNS, then 222,750 children and their families could still obtain much needed relief in the US alone—and 100,000s more worldwide. Our imaging studies could, moreover, improve TNS by uncovering where it acts in the brain, which imaging measures are changed by it, and which portend favorable response. If, in contrast, TNS is not safe or effective for PAE, it will still be impactful to demonstrate to clinicians that PAE is a negative prognostic factor when treating patients with TNS.

### Specific Aims

1. **Aim 1 Conduct a 4-Week Open Trial of Nightly TNS** (30/24 children pre/post-attrition aged 8-12 yr with PAE) **to test feasibility of TNS.** *We hypothesize TNS will be feasible (safe, well-tolerated, promising clinical efficacy) for pediatric PAE.*
2. **Aim 2 Acquire MRI, magnetic resonance spectroscopy (MRS), diffusion tensor imaging (DTI), and resting-state functional magnetic resonance imaging (rsfMRI) of the brain before and after TNS.** *In anterior cingulate cortex (ACC), middle frontal cortex (MFC), and inferior frontal cortex (IFC), we hypothesize that mean glutamate (Glu) levels will increase and functional connectivity (fc) will decrease after TNS. Pre-TNS, low local gyrification index (LGI), myelin, and Glu and high mean diffusivity (MD) and fc in these regions will predict favorable post-TNS response, including diminished hyperactivity/impulsivity, increased attention, and improved executive function.*

### Hypotheses:

Aim 1: TNS will be feasible (safe, well-tolerated, promising clinical efficacy) for pediatric PAE.

Scores on all behavioral measures will move from the clinical to the nonclinical range. For example, a T score moving from 1 ½ standard deviations above the mean of 50 to less than 1 ½ standard deviations will indicate clinical efficacy

Aim 2: Mean Glu will increase and fc will decrease after TNS. Pre-TNS, low LGI, myelin and Glu and high MD and fc in ACC, MFC, and IFC will predict favorable post-TNS response.

**Subjects:** Prenatal alcohol exposure (PAE)

Inclusion:

Cohort 1: “PAE”

- Fetal alcohol syndrome, partial fetal alcohol syndrome, or alcohol-related neurodevelopmental disorder per modified Institute of Medicine criteria (thus positive maternal drinking in pregnancy required, facial stigmata not required)
- PAE >6 drinks/week for  $\geq 2$  weeks and/or  $\geq 3$  drinks on  $\geq 2$  occasions throughout gestation per Health Interview for Women/Health Interview for Adoptive and Foster Parents (HIW/HIAFP)
- Diagnosis of DSM-5 ADHD, including problems with inattention, hyperactivity, impulsivity, and/or executive function. Screening for ADHD will be done using the SNAP IV. Formal diagnosis of ADHD will be based on the MINI-KID with input from the Behavior Rating of Executive Function (BRIEF II) and the Conners 4.
- Parent and child able to complete testing in English
- Child able to cooperate during MRI
- Full-Scale IQ >70 per K-BIT-2
- Child able to comply with study procedures
- Age 8-12

Exclusion

- Other toxic exposure per HIW/HIAFP whose influence clearly surpasses that of alcohol (very rare) per study clinician (Drs. [name], [name], or delegate) judgement
- Known genetic syndrome associated with ADHD-like symptoms including fragile X, tuberous sclerosis, or generalized resistance to thyroid hormone
- Serious medical or neurologic illness likely to influence brain function, e.g., seizures, closed-head trauma
- Gestation <34 weeks
- Ferromagnetic metal, claustrophobia, or other MRI or TNS contraindication (e.g., insulin pumps or other body-worn devices)
- Diagnosis of autism spectrum disorder, psychotic disorder, or major mood disorder
- Active suicidal ideation as evidenced by meeting criteria for “Current” or “Lifetime attempt” on the Suicidality module or “Current” or “In early remission” on the Suicide Behavior Disorder module of the MINI KID

Note on Medication

- Given frequent prescription of psychotropic medication in this population, recruiting exclusively unmedicated children is not feasible. Therefore, medication will be allowed in this study, but its use will be recorded. Patients currently on stimulant medication will be asked to withhold medication on assessment days.

The study team will make use of a checklist of Inclusion/Exclusion criteria when making the enrollment decision for each participant. The study team will also maintain a CONSORT-type diagram of participant screenings, exclusion, enrollment, retention, and dropout throughout the study. Data will specify reasons for study exclusion and dropout. Data from subjects excluded at screening will be fully anonymized; personal health information from these subjects will be destroyed.

**Sample size:** 30 PAE pre-attrition (24 post-attrition)

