Conners 4 Parent Version (Conners 4 P; Conners 2022)— The Conners 3 Parent Version originally proposed for this study to measure symptoms of ADHD is no longer available and has been replaced with the Conners 4 Parent Version (Conners 4 P) which provides a comprehensive assessment of symptoms and impairments associated with ADHD and common co-occurring problems and disorders in children and youth aged 6 to 18 years. The Conners 4 P is an inclusive and standardized measure that builds on the strengths of the Conners Rating Scales. Now fully digital, it provides online scoring for better data visualization, easy inventory management, a digital manual, and printable forms. It addresses critical concerns with Conduct and Self-Harm items and a Sleep Problems indicator. It also evaluates new content areas and common co-occurring problems such as Emotional Dysregulation, Depressed Mood, and Anxious Thoughts. Finally, the Conners 4 P provides a more comprehensive picture of how a rater approaches completing the measure, using new and updated validity scales, the number of omitted items, and the average number of items completed per minute. The Conners 4 P has excellent internal consistency (median omega coefficient = 0.94), strong test-retest reliability (median  $r = 0.89$ ), and convergent validity (median  $r = 0.73$ ). The parent completes the Conners 4 P before and after treatment.

Behavior Rating Inventory of Executive Function (BRIEF II) (Gioia et al. 2000)—The BRIEF II is a validated assessment of executive functions for children and adolescents that is very widely used clinically and in research. It is administered to parents before and after treatment by a Study Researcher. It takes 10-15 min. We use it to assess severity of executive function symptoms in children with PAE at baseline and after the TNS treatment regimen.

NIH Toolbox (Gershon et al. 2010)—The NIH Toolbox is a multidimensional set of measures to assess neurological and behavioral function available for clinicians and researchers. It is a valid, reliable, brief, and state-of-the-art instrument. We administer only the Cognition and Emotional Control Batteries to our pediatric patients. The latter assess domains of the PAE behavioral phenotype in DSM-5. (The primary author of this section of the DSM-5 is Co-I [name].) The Cognition Battery yields Cognitive Function Composite, Fluid Cognition Composite (Dimensional Change Card Sort, Flanker Inhibitory

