Delis-Kaplan Executive Function System (D-KEFS) Verbal Fluency (Delis et al. 2001,2004)—Unpublished data from our recent study of PAE (NIAAA R01AA025066) show significantly inferior performance ( $p < 0.001-0.041$ ; effect sizes 0.4-1.2) on 7/9 tests of the D-KEFS Verbal Fluency assessment. This is consistent with many prior reports of verbal fluency deficits in PAE (Iosub et al. 2018, Kingdon et al. 2016, Kodituwakku et al. 2006, Kovács et al. 2023, Mattson & Riley 1999, Panczakiewicz et al. 2018, Rassmussen & Bisanz 2009, Schonfeld et al. 2001, Vaurio et al. 2008). There are indications that disability in verbal fluency is mediated by executive function deficits (Doyle et al. 2018). TNS, as mentioned elsewhere in this proposal, improves executive function deficits in children with ADHD. We will administer the D-KEFS Verbal Fluency assessment to determine whether TNS induces improvement in verbal fluency. The D-KEFS Verbal Fluency Test is comprised of three testing conditions: Letter Fluency, Category Fluency, and Category Switching. This test measures multiple aspects of verbal behavioral productivity and cognitive flexibility. It evaluates effectiveness of novel and semantic search strategies, and assesses flexibility in the implementation of semantic search strategies. The process approach enables further evaluation of self-monitoring of information search, as well as difficulties related to initiation and sustaining effort. There are three conditions in the Verbal Fluency test in which the examinee must say as many words as they can by letter, category, and category switching prompts. 1. The examinee says words beginning with a specified letter as quickly as possible; 2. The examinee is asked to say words belonging to a designated semantic category; and 3. The examinee must alternate between saying words from two different; semantic categories. The test will be administered by the Study Coordinator or SRA I to the child.

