#### Measurements:

1. Primary outcome: Score on the ADHD-RS, a clinician-rated measure of severity of core symptoms of ADHD; administered pre- and post-TNS
2. Secondary outcome: Score on the CGI-S/CGI-I ADHD, clinician-rated measures of severity of core symptoms of ADHD; CGI-S is administered pre-TNS and CGI-I is administered post-TNS
3. Magnetic Resonance Imaging: multiple modalities and endpoints, acquired pre- and post-TNS

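### The Aim 1 efficacy statement (all behavioral measures leaving the clinical range) does not match the primary outcome or analysis, cannot be met on some measures, and sets no minimum change

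*Protocol*

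**What the plan says.** Protocol, Hypotheses, Aim 1: "Scores on all behavioral measures will move from the clinical to the nonclinical range". The next sentence offers an example, "a T score moving from 1 ½ standard deviations above the mean of 50 to less than 1 ½ standard deviations", and ends by saying that such a move in "standard deviations will indicate clinical efficacy". With the usual T-score SD of 10, which the protocol does not state, that line is T = 65. The text does not define the behavioral measures, does not say whether scores means each child's score or the group mean, and sets no minimum size of change.

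Protocol, Measurements: the primary outcome is "Score on the ADHD-RS, a clinician-rated measure of severity of core symptoms of ADHD", taken before and after treatment. The secondary outcome is the CGI, with CGI-S before treatment and CGI-I after it.

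Protocol, Data Analysis: mean differences are tested in a linear mixed model. Range-crossing is not mentioned.

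Protocol, Inclusion and Exclusion: an ADHD diagnosis is required, but no T-score floor is set on any outcome scale. One exclusion is "Diagnosis of autism spectrum disorder, psychotic disorder, or major mood disorder". On the diagnosis, the inclusion list says "Formal diagnosis of ADHD will be based on the MINI-KID with input from the Behavior Rating of Executive Function" (the BRIEF II) and the Conners 4. Research Protocol items 2 and 3, by contrast, confirm ADHD with the MINI-KID at the eligibility step and give the BRIEF II and Conners 4 afterwards, to children already found eligible.

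**The concern.** Aim 1 counts promising clinical efficacy as part of feasibility, and this is the only place where the protocol attaches a number to efficacy. If that number belongs to a different rule from the declared outcome and analysis, the report can follow whichever looks better once the data are in. The rule can also mislead in both directions. It can fail when treatment works, because some measures have no clinical range to leave or no way to leave it. It can appear met when nothing has changed, because a one-point move across a line is enough and a single-arm trial has no comparison group to show how often that happens untreated.

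**Working it through.** The protocol gives no power, response rate or threshold calculation for this statement, so there is no figure to reproduce. The check has three parts.

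**1. Consistency between sections**

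| Section | Measure | What is judged |
|---|---|---|
| Hypotheses, Aim 1 | all behavioral measures | crossing from clinical to nonclinical |
| Measurements | ADHD-RS (primary) | score before and after |
| Data Analysis | not restricted | mean differences |

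A clear mean fall on the ADHD-RS while the CDI 2 stays where it was is a success by the second and third rows and a failure by the first. Small falls that take mean T scores just under 65, with a mean ADHD-RS change that cannot be told from zero, would give the reverse on those scales.

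**2. Whether the statement can be met**

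- *Starting nonclinical.* No outcome has an entry floor. A child below the line at week 0 cannot move out of the clinical range. Excluding major mood disorder makes this more likely on depression scores; the protocol gives no baseline rates.
- *CGI.* CGI-S is given only before treatment and CGI-I only after. They are different scales, so no movement between ranges can be computed.
- *Measures where higher is better.* On D-KEFS Verbal Fluency "the examinee must say as many words as they can", so impairment lies below the mean. The same holds for NIH Toolbox cognition and for Positive Affect. No cut-off or direction is given for these.
- *Illustration for D-KEFS.* The protocol reports effect sizes of 0.4 to 1.2 in PAE. Read as SD units, with normal scores, unit SD and a line 1.5 SD below the mean (all assumptions), the share starting beyond the line is Φ(−1.5 + 0.4) = 14% to Φ(−1.5 + 1.2) = 38%. Between 62% and 86% would have no clinical range to leave.

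**3. Noise, if the statement is read per child**

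Inputs: r = 0.89, the median test-retest correlation for the Conners 4 P (Pre-TNS Assessments; the retest interval is not given). SD 10 and the group means are assumptions.

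- SE of a difference = SD × √(2(1 − r)) = 10 × √0.22 = 4.69 points.
- 95% reliable-change limit = 1.96 × 4.69 = 9.2 points. It is 12.4 at r = 0.80 and 6.2 at r = 0.95.
- With no true change, a child observed at x retests as Normal with mean μ + r(x − μ) and SD 10 × √(1 − 0.89²) = 4.56.
- x = 66, μ = 72: mean 72 + 0.89 × (−6) = 66.66; P(below 65) = Φ((65 − 66.66)/4.56) = Φ(−0.364) = 36%.
- x = 70, μ = 70: Φ(−1.097) = 14%.
- x = 75, μ = 70: mean 74.45; Φ(−2.07) = 2%.

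For all children starting at 65 or above, with test and retest bivariate normal and no true change:

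| Assumed group mean | Cross by chance | Expected among 24 such children |
|---|---|---|
| 68 | 11.7% | 2.8 |
| 70 | 9.6% | 2.3 |
| 72 | 7.7% | 1.9 |
| 75 | 5.4% | 1.3 |

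Requiring the fall also to exceed 9.2 points cuts these rates to 1.7% at group mean 68 and 0.8% at 75 (simulation of 2 million pairs). In the other direction, a fall from 85 to 66 is 19 points, about twice the limit, and does not count.

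**The case against.** The sentence is a hypothesis in an open feasibility pilot, not a formal success rule, and the protocol already has a separate primary outcome and analysis. That stands, and it is why the remedy is a matter of wording. But the protocol says that the crossing will indicate clinical efficacy, and that claim conflicts with its other sections.

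A reader might go further in five ways that the documents do not support.

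- *That the criterion points the wrong way on D-KEFS and similar tests.* The 1.5-SD line is introduced as an example and for a T score; the general sentence has no direction. The fault is that no cut-off or direction is given for those measures.
- *That crossings are mostly noise.* They are a minority: about 5% to 12% at r = 0.89, concentrated just above the line. The figures apply only per child. If scores means group means, the SE of a mean change in 24 children from retest error alone is about 4.69/√24 = 0.96 points and single-child noise matters much less. The protocol does not say which reading is meant.
- *That the rule decides whether the R33 is sought.* The Project Summary ties the next phase to feasibility: compliance, serious side effects, an indication of symptom relief, and its retention. Nothing ties it to range-crossing.
- *That children mostly cannot start in the clinical range on the RCADS.* Five of its six subscales concern anxiety, which the mood-disorder exclusion does not touch, and no baseline rates are given.
- *That removing the BRIEF II and Conners 4 from the diagnosis would cure regression to the mean.* Selection on other, correlated ADHD measures would leave it in place. What remains is a contradiction between two sections about when those scales are used.

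Reliable-change limits and confidence intervals may sit in a statistical analysis plan that is not at hand. Their absence is not the fault; the conflicting rule that the protocol does state is.

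**Conclusion.** The point holds: the Aim 1 efficacy statement is wrongly fixed and should be corrected before outcomes are read. The mismatch with Measurements and Data Analysis, and the measures on which the statement cannot be met or computed, rest on the text alone and hold under either reading of scores; only counting the CGI among the undefined behavioral measures is a matter of reading. The noise argument is of moderate size and conditional: it needs the per-child reading, SD 10, assumed group means of 68 to 75, and one scale's median retest correlation carried over to an interval of about five weeks. On those terms about 1 to 3 of 24 children starting in the clinical range would be expected to cross with no true change, and the single-arm design cannot reveal it.

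**What to change.** In Hypotheses, Aim 1, state that efficacy is judged on the mean change in ADHD-RS score from week 0 to week 5, with its 95% CI. This agrees with Measurements and Data Analysis.

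Keep range-crossing only as a secondary description, reported separately for each measure:

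- among children in the clinical range on that measure at week 0;
- with that measure's own cut-off and impaired direction stated;
- counted only when the change also exceeds the measure's reliable-change limit, about 9.2 T points for the Conners 4 at r = 0.89 and SD 10.

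Leave the CGI out of the range-crossing description, since its two forms cannot be compared in this way.

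Separately, reconcile the inclusion criterion, which gives the BRIEF II and Conners 4 a part in the ADHD diagnosis, with the Research Protocol, which gives them only after eligibility.

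The cost is protocol wording; no assessment or visit changes. The responder count will be somewhat lower than under the present rule.
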